### 1.1.6 Study Population

A minimum of 39 and 30 subjects will be included in the RIFT-HPV 1 and 2 study cohorts respectively, according to inclusion and exclusion criteria described in section 5.

All study activities listed in section 1.2.2 will be performed on RIFT-HPV 1 and 2 cohorts.

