### 2.2.7 Benefit/Risk Assessment

The 9vHPV vaccine has been shown to be beneficial and efficacious in preventing persistent anogenital HPV infection and disease associated with the 9 HPV types (6, 11, 16, 18, 31, 33, 45, 52, and 58). The frequency, severity, and magnitude of AEs identified in previous studies and post-marketing surveillance support a favorable benefit-risk analysis for the 9vHPV vaccine in the study population. In this study, the 9vHPV vaccine will be administered in the same 3-dose regime as currently used for the vaccination of girls through the Spanish National HPV Immunization Program^38.

Study subjects will benefit from participating in the study by receiving the 9vHPV vaccine, which is currently not included in the Spanish National Immunization Program for adult women. Although vaccination is unable to eliminate HPV infections already present, most HPV infections are cleared after 12-24 months, thus vaccination with 9vHPV will confer protection for future HPV persistent infections in women enrolled in the study.

Study subjects will also benefit from a gynecological examination by trained and experienced medical personnel, who may refer her for appropriate care and treatment.

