## 5.1 INCLUSION CRITERIA

Candidates are eligible for inclusion in the study if they:

- Are women, aged 18 years or older for cohort 1 and cohort 2 , attending a routine cervical cancer screening visit or gynecological visit, are positive for HPV16 and/or HPV18 have been recently diagnosed for their HPV-positivity (within the last 10 months) and meet one of the following criteria:

**RIFT-HPV 1 cohort:** non-vaccinated adult women aged 18 years or older, positive on cervix for HPV 16 and/or 18, with non apparent cervical lesion or with cervical intraepithelial neoplasia (CIN) 1/2 lesion on cytology or biopsy, eligible for **conservative treatment**.

**RIFT-HPV 2 cohort:** non-vaccinated adult women aged 18 years or older, positive for HPV 16 and/or HPV 18 anal test with non-apparent anal lesions or with anal lesions eligible for **conservative treatment**. Or non-vaccinated adult women aged 18 years or older, positive for HPV 16 and/or HPV 18 cervical test with vulvar premalignant lesion or condylomas, associated to HPV infection.

- Are judged to have no major health conditions (based on medical history, physical examination, and laboratory testing) that may compromise their capacity to comply with study procedures, as per Investigator's judgement.
- Provide written informed consent for their participation in the study.
- Provide a frequent contact telephone number as well as an alternate means of contact (such as an alternate telephone number or email) for follow-up purposes.
- Are planning to stay in their area of residence (near the study site) for the full duration of the study, so it is convenient for them to attend study visits at the site.

The following conditions ARE NOT CONSIDERED EXCLUSION CRITERIA. Therefore, candidates complying with them ARE ELIGIBLE FOR INCLUSION in the study:

- Coinfection with others HPV genotypes
- History of cervical surgery.
- History of condyloma acuminata
- History of HIV or other immunosuppressive conditions either acquired or medically induced.
- History of transplant immunosuppression.
- History of an autoimmune disease.

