##### 9.1.1.1.2 *Inclusion in the analysis population*

The below criteria will be followed to include cases in the analysis population:

Before vaccination (Visit 1):

- HPV16/18/16+18 positive DNA detection and genotyping (using Anyplex HPV28) in collected cervical, anal, urine, vulvar and oral samples.
- HPV16/18 positive virion detection (using ELISA, electronic microscopy) in collected cervical, anal, urine, vulvar and oral samples.

Therefore, cases showing:

- negative HPV16/18 DNA test and/or
- absence of HPV16/18 viral particles,

will not be included in the analysis population.

After vaccination (Visits 2 to 4, Months 2, 6 and 7):

- HPV16/18/16+18 positive DNA detection and genotyping (using Anyplex HPV28) in collected cervical, anal, urine, vulvar and oral samples.
- HPV16/18 positive virion detection (using ELISA, electronic microscopy) in collected cervical, anal, urine, vulvar and oral samples.
- Positive detection of exudated HPV 6/11/16/18/31/33/45/52/58 L1 antibodies in collected cervical, anal, urine, vulvar and oral samples.
- Positive detection/titration of HPV 6/11/16/18/31/33/45/52/58 L1 antibodies in collected serum samples (positive seroconversion).

Therefore, cases showing:

- negative HPV16/18 DNA test and/or
- absence of HPV16/18 viral particles and/or

- absence of exudated HPV L1 antibodies and/or
- absence of positive seroconversion,

will not be included in the analysis population.

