##### **9.1.2.1.2 Inclusion in the analysis population**

All cases showing positive seroconversion for HPV16/18/16+18 will be included.

For each HPV type analyzed, proportion of seroconverted cases after 3 vaccine doses (Month 7/ Visit 4) will be provided.

It is expected that 90% of cases show positive seroconversion after 3-dose 9vHPV vaccination.

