## 9.2 Sample Size and Power

### 9.2.1 RIFT-HPV 1 cohort

The sample size for this cohort has been calculated based on the demonstration of viral infectivity reduction before and after a 3-dose regimen of 9vHPV vaccination in cervical samples as a reference.

Accepting an alpha risk of 0.05 and a beta risk of less than 0.2 in a bilateral contrast, it has been estimated that a minimum of 39 women fulfilling the 3-dose vaccination schedule is needed to detect a difference equal to or greater than a 25% infectivity reduction in cervical samples.

It has been estimated a 40% sampling loss from those study subjects:

- showing an HPV16/18/double 16-18 positive result not confirmed by Anyplex HPV28,
- not fulfilling the 9vHPV 3-dose schedule,
- showing HPV clearance at Month 7 visit,
- showing a non-productive infection before vaccination.

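### The 40% loss estimate in 9.2.1 leaves out post-vaccination exclusions imposed by 9.1.1.1.2; on the plan's own seroconversion figure it should be about 46%, at a cost of 4 to 5 points of power

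*Protocol*

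**What the plan says.** Protocol 9.2.1 sets the cohort 1 requirement for the cervical analysis, with a two-sided alpha of 0.05 and power of at least 80%: "a minimum of 39 women fulfilling the 3-dose vaccination schedule is needed to detect a difference equal to or greater than a 25% infectivity reduction". The section then gives a loss estimate: "It has been estimated a 40% sampling loss from those study subjects". Four reasons follow: a positive result that Anyplex does not confirm, an incomplete three-dose schedule, clearance at Month 7, and a non-productive infection before vaccination. The 40% is not split between them.

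Section 9.1.1.1.2 defines who enters the primary analysis. After vaccination it removes cases on any of four grounds: a negative HPV16/18 DNA test, no viral particles, no antibody in the mucosal sample ("absence of exudated HPV L1 antibodies and/or" in the list), and no seroconversion.

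Section 9.1.2.1.2 gives a rate for the last of these: "It is expected that 90% of cases show positive seroconversion after 3-dose 9vHPV vaccination".

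On enrolment, section 1.1.6 states: "A minimum of 39 and 30 subjects will be included in the RIFT-HPV 1 and 2 study cohorts respectively". Section 4.1 repeats those minimums. Section 5.3 says that women who discontinue vaccination or withdraw are not replaced.

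**The concern.** A loss estimate is useful only if it covers every route by which an enrolled woman can drop out of the primary analysis. Of the four post-vaccination grounds in 9.1.1.1.2, only the negative DNA test clearly matches an item in 9.2.1 (clearance). Absent exudated antibody and absent seroconversion match nothing. Absent virions are counted only before vaccination.

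The loss figure is what links enrolment to the 39 women on whom the 80% power rests. If it is too low, enrolment planned from it yields fewer than 39, and the trial has less power for a 25% reduction than 9.2.1 suggests.

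**Working it through.** **Matching the two lists**

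- Negative DNA after vaccination (9.1.1.1.2): covered in 9.2.1 as clearance.
- No virions after vaccination: not listed, unless clearance, which is undefined, is stretched to cover it.
- No exudated antibody: not listed, and no rate is given anywhere.
- No seroconversion: not listed; 9.1.2.1.2 implies 10% failure among women given three doses.

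**The plan's own 39**

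This cannot be reproduced, because no standard deviation of the paired difference is given. It can only be back-solved. With n = 39, a 25% reduction, two-sided alpha 0.05 and 80% power, a paired t-test needs a standardised effect of 0.460, so the implied SD is 0.25 / 0.460 = 0.54. The normal approximation gives 0.56, and a Wilcoxon efficiency of 3/π gives 0.53. Everything below holds the effect at 0.460, so it is conditional on 39 evaluable women giving 80%.

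**Loss with the one omitted exclusion that has a rate**

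Assuming the 10% is independent of the 40%: retained share = 0.6 × 0.9 = 0.54; loss = 46%.

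**Power**

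Power is the probability that a noncentral t with n − 1 degrees of freedom and noncentrality 0.460 × √n exceeds the 0.975 quantile of the central t.

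*If enrolment were inflated for the stated 40%:*

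- Enrolment = 39 / 0.6 = 65.
- Evaluable after all losses = 65 × 0.54 = 35.1, so 35.
- Power at 35: about 75% (0.754; the Wilcoxon efficiency gives 0.753).
- Enrolment needed to keep 39 evaluable = 39 / 0.54 = 72.2, so 73.

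*At the planned minimum of 39 enrolled:*

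- With the 40% alone: 39 × 0.6 = 23.4, so 23 evaluable; power about 56%.
- With the omitted 10% as well: 39 × 0.54 = 21.1, so 21 evaluable; power about 52%.
- Reduction detectable with 80% power, at the implied SD of 0.54: 33.2% with 23 and 34.9% with 21.

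The omission therefore costs 80 − 75 = 5 points on the first basis, and 56 − 52 = 4 points of power with 34.9 − 33.2 = 1.7 points of detectable reduction on the second.

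**Range for the two exclusions without a rate**

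The rates here are assumptions. Each is applied to both exclusions, independently, on top of the 10%. Evaluable numbers are out of 65 enrolled:

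- 5% each: 0.54 × 0.95² = 0.487 retained (51% lost); 31 evaluable, power about 70%; 81 enrolled needed for 39.
- 10% each: 0.54 × 0.9² = 0.437 retained (56% lost); 28 evaluable, power about 65%; 90 needed.
- 20% each: 0.54 × 0.8² = 0.346 retained (65% lost); 22 evaluable, power about 54%; 113 needed.

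**The case against.** Several objections have force.

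- **No evaluable number net of loss is stated.** Section 9.2.1 says how many completers are needed, and power given 39 evaluable women does not change with the loss rate. This stands: the fault lies in the loss estimate and in what enrolment delivers, not in a stated evaluable count.
- **The 10% may be too high.** The 90% is an expectation for the antibody objective. Section 9.1.4 counts a natural antibody response as positive, and all participants are HPV-positive. This stands, so a reader should not take 46% as a floor. Failure to seroconvert may also overlap with the listed losses and with absent exudated antibody. Still, 90% is the only planning figure the protocol offers.
- **Clearance might include loss of virions.** That would leave two omitted exclusions rather than three. Section 9.1.4 defines persistent infection and productive infection separately, which speaks against this reading but does not exclude it.
- **The 39 might already allow for the 40%.** If 23 evaluable women were what gives 80%, the further 10% would leave 20 or 21 and power of about 74 to 76%. The text does not favour this, since 39 is given as the number completing the schedule, but the omission costs a similar amount.

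Two stronger inferences are tempting and unsupported. A reader might blame the omission for the whole fall from 80% to 52% power, or for the move from 25% to 35%. Most of that fall, to 56% and 33%, is present before any omitted exclusion is counted, because the 40% is not applied to the 39 enrolled. A reader might also combine "most HPV infections are cleared after 12-24 months" with diagnoses up to 10 months old (5.1) to argue that clearance alone uses up the allowance. Clearance is already a listed reason, and the protocol gives neither a median nor a curve from which a seven-month rate could be derived.

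**Conclusion.** The loss estimate in 9.2.1 is incomplete against the protocol's own analysis rule. Two post-vaccination exclusions are clearly missing and a third arguably is. On the one rate the plan supplies, the loss is about 46% instead of 40%. The omission itself is of moderate size, and the larger shortfall at 39 enrolled is the uninflated enrolment.

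The result rests on four assumptions: 39 evaluable women give 80% power; a paired t-test stands in for the planned Wilcoxon signed rank test; the 10% is independent of the 40%; and enrolment stops at the stated minimum of 39 or at the inflated 65. The direction does not depend on the exact figures: any omitted loss not already inside the 40% lowers the evaluable number at a given enrolment.

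**What to change.** In 9.2.1, restate the loss so that it covers every exclusion in 9.1.1.1.2. Give about 46% when seroconversion failure alone is added, with independence stated as an assumption, and a stated range for absent exudated antibody and absent post-vaccination virions. Say whether clearance includes loss of virions. State enrolled and evaluable numbers separately, give the SD behind the 39, and report the power and the detectable reduction at the planned enrolment.

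The cost is recalculation and wording, and the stated figures become less favourable. No extra participants are needed if the lower power is accepted. Keeping 39 evaluable would take 73 enrolled, against 65 for the 40% alone, before the exclusions without a rate. Dropping the post-vaccination antibody and virion filters would also remove the extra loss, but that changes the primary analysis population and should be decided on its own merits.

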### 9.2.2 RIFT-HPV 2 cohort

The sample size for this cohort has been calculated based on the demonstration of viral infectivity reduction before and after a 3-dose regimen of 9vHPV vaccination in anal samples as a reference.

Accepting an alpha risk of 0.05 and a beta risk of less than 0.2 in a bilateral contrast, it has been estimated that a minimum of 28 positive women with multiple anogenital lesions, with an HPV-positive anal sample and fulfilling the 3-dose vaccination schedule is needed to detect a difference equal to or greater than a 35% reduction in infectivity in anal samples.

It has been estimated that:

- more than 60% of study subjects with multiple anogenital infection will show HPV positivity in anal samples.
- at least 28% of study subjects with HPV cervical infection will also show anal infection.
- subjects from the RIFT-HPV 1 cohort will also show anal infection, thus increasing the RIFT-HPV 2 cohort size.

Considering these estimations, it is necessary to enroll 30 subjects in RIFT HPV 2 cohort to detect 18 subjects with anal infection, which added to the 10 subjects with anal infection from the RIFT-HPV 1 cohort, gives a total number of 28 subjects needed to evaluate differences in viral infectivity of anal samples.

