## 4.2 SCIENTIFIC RATIONALE FOR STUDY DESIGN

### 4.2.1 Rationale for Study Population

The study population is composed of two different cohorts.

**The RIFT-HPV 1 cohort.** It includes non-vaccinated adult women aged 18 years or older, positive on cervix for HPV 16 and/or 18 with non-apparent cervical lesion or with cervical intraepithelial neoplasia (CIN) 1/2 lesion on cytology or biopsy, eligible for **conservative treatment**.

Eligible women for this cohort are expected to frequently have productive cervical HPV infections (i.e., with high production of virions capable of infecting new cells) that allow the evaluation of HPV infectivity in cervical samples using the E1+E4-HaCaT essay, before and after vaccination with 9vHPV in a three-dose regimen.

Women in this cohort are generally expected to have a low prevalence of anal HPV infections (5% to 22% in women with no HPV-related pathology) and therefore, the obtention of anal samples with productive HPV infections is expected to be scarce.

**The RIFT-HPV 2 cohort.** It includes non-vaccinated adult women aged 18 years or older, positive for HPV 16 and/or HPV 18 anal test with non-apparent anal lesions or with anal lesions eligible for **conservative treatment**. Or non-vaccinated adult women aged 18 years or older, positive for HPV 16 and/or HPV 18 cervical test with vulvar premalignant lesion or condylomas, associated to HPV infection.

Eligible women for this cohort are expected to frequently have productive cervical and anal HPV infections that allow the evaluation of HPV infectivity in cervical, vulvar and anal samples using the E1+E4-HaCaT essay, before and after vaccination with 9vHPV in a three-dose regimen.

Since anal HPV infections are more prevalent in women with HPV-related cervical or vulvar/vaginal lesions (23% to 86%), this second study cohort will guarantee the obtention of anal and vulvar samples with productive HPV infections.

Oral and urine samples will be obtained from study subjects belonging to both study cohorts. HPV infectivity in oral and urine samples with productive HPV infections will be also evaluated in the same conditions as cervical, vulvar and anal samples.

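### Section 9.2.2 counts 28 baseline anal-positive women as 28 evaluable pairs with no allowance for loss, so the stated 80% power for a 35% reduction is not supported

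*Protocol*

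**What the plan says.** Section 9.2.2 sizes RIFT-HPV 2 on the anal comparison: "Accepting an alpha risk of 0.05 and a beta risk of less than 0.2 in a bilateral contrast", it wants to detect "a difference equal to or greater than a 35% reduction in infectivity in anal samples". The requirement is that "a minimum of 28 positive women with multiple anogenital lesions, with an HPV-positive anal sample and fulfilling the 3-dose vaccination schedule is needed".

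The supply side uses two rates. For RIFT-HPV 2, "more than 60% of study subjects with multiple anogenital infection will show HPV positivity in anal samples". For RIFT-HPV 1, "at least 28% of study subjects with HPV cervical infection will also show anal infection". Enrolling 30 is said to yield 18 women with anal infection, "which added to the 10 subjects with anal infection from the RIFT-HPV 1 cohort, gives a total number of 28 subjects needed".

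Other parts of the protocol bear on this count:

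- Section 9.2.1 estimates a 40% loss for RIFT-HPV 1, from HPV results not confirmed by the study assay, incomplete dosing, clearance by Month 7 and non-productive infection at baseline. Section 9.2.2 states no loss.
- Section 9.1.1.1.2 admits a case only with HPV16/18 DNA and virions before and after vaccination, and with local antibody and seroconversion afterwards. This covers anal samples as well as cervical ones.
- Section 5.3 says women who stop vaccination or withdraw are not replaced.
- Section 4.2.1 expects RIFT-HPV 1 women to have a "low prevalence of anal HPV infections (5% to 22% in women with no HPV-related pathology") and productive anal samples to be scarce. It also gives 23% to 86% for women with HPV-related cervical or vulvar/vaginal lesions.
- The end of section 4.2.1 gives 28 as the minimum to include in the second cohort. Sections 1.1.6 and 9.2.2 enrol 30, and 9.2.2 makes 28 the anal count pooled over both cohorts.

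**The concern.** The requirement and the supply are different quantities. The 28 that carries the power is a number of completers with a usable before-and-after pair. The 28 that the plan expects to find is a number of women infected at baseline. Setting one equal to the other assumes that every anal-positive woman completes dosing, stays infected, has a productive infection and passes the antibody conditions. Section 9.2.1 plans on the opposite for cervical samples.

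Anal samples are part of the primary objective, and the anal comparison is the only basis given for the size of RIFT-HPV 2. If the evaluable number falls well short, a null anal result could be read as coming from an adequately powered comparison when it did not.

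**Working it through.** **Inputs.** Two-sided alpha 0.05, power at least 80%, a 35% reduction, 28 pairs, rates of 60% and 28% (9.2.2). Enrolment of 39 and 30 (1.1.6). A 25% reduction with 39 pairs and 40% loss for RIFT-HPV 1 (9.2.1). A paired signed-rank test at Visit 1 against Visit 4, anal samples pooled over cohorts (9.1.1.2).

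**Step 1: reproduce the 28.** 30 x 0.60 = 18.0. 39 x 0.28 = 10.92, taken as 10. The sum is 28, so the head count reproduces. Unrounded it is 28.92, and 28 / 28.92 = 0.968, so a loss above about 3% misses the target.

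**Step 2: apply a loss.** Evaluable pairs = 28 x (1 - loss): 25.2 at 10%, 22.4 at 20%, 19.6 at 30%, 16.8 at 40%. Keeping 28 after a 40% loss would need 28 / 0.6 = 46.7, that is 47 anal-positive women at baseline.

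The 39 can also be read as net of loss, because 9.2.1 defines it as women completing three doses. Then only the RIFT-HPV 2 part shrinks: 18 x 0.6 + 10.92 = 10.8 + 10.92 = 21.7, about 21 pairs.

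**Step 3: convert to power.** No SD of the paired difference is given, so the 28 cannot be derived from first principles. Two calibrations come from the protocol's own figures, here by the normal approximation with 1.960 + 0.842 = 2.802:

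- A: 28 pairs give exactly 80%. The standardised effect is 2.802 / sqrt(28) = 0.529, so the SD is 0.35 / 0.529 = 0.66.
- B: 39 pairs give exactly 80% for a 25% reduction. The effect is 2.802 / sqrt(39) = 0.449, so the SD is 0.25 / 0.449 = 0.557. For 35% the effect becomes 0.35 / 0.557 = 0.628. This assumes that anal and cervical differences share a scale and an SD.

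Power is approximately Phi(effect x sqrt(n) - 1.960). At n = 17 under A: 0.529 x 4.123 - 1.960 = 0.22, so 59%. Under B: 0.628 x 4.123 - 1.960 = 0.63, so 74%. The ranges below also cover the noncentral t and the t with the Wilcoxon efficiency of 3/pi.

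| Pairs | How reached | Power, A | Power, B |
|---|---|---|---|
| 28 | as planned | 80% | about 91% |
| 26 | 22% anal rate in RIFT-HPV 1, no loss | 77% | 88-89% |
| 21 | 40% loss in RIFT-HPV 2 only | 67-68% | 80-82% |
| 20 | 5% anal rate in RIFT-HPV 1, no loss | 64-66% | 78-80% |
| 17 | 40% loss in both cohorts | 57-59% | 70-74% |

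The reduction detectable with 80% power (normal approximation) at 17 pairs is 35% x sqrt(28/17) = 45% under A and 25% x sqrt(39/17) = 38% under B. At 21 pairs it is 40% and 34%.

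**Step 4: the RIFT-HPV 1 anal rate.** At 5%, 39 x 0.05 = 1.95; at 22%, 39 x 0.22 = 8.58. With the 18 from RIFT-HPV 2 this gives 19.95 to 26.58, about 20 to 26 pairs before loss, against the planned 28.

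**Step 5: the RIFT-HPV 2 rate.** The 60% refers to multiple anogenital infection. Section 5.1 admits women either on a positive anal HPV16/18 test, or on a positive cervical test with a vulvar premalignant lesion or condylomas. The 60% matches neither route. It may be too low for the first, and its fit to the second is not stated.

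**The case against.** A reader might infer that the 28% rate contradicts section 4.2.1. The documents do not go that far. The 5-22% range is quoted for women with no HPV-related pathology, the same section gives 23-86% for women with lesions, and RIFT-HPV 1 admits CIN 1/2. So 28% lies inside one of the two ranges that could apply to a mixed cohort. Section 4.2.1 does attach the low range to this cohort, so the passages are unreconciled. Still, only 10 of the 28 rest on this rate, and under calibration B the drop to 26 pairs leaves power well above 80%.

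A reader might also infer that the power is shown to fail. It is not. No SD is stated, the rates and enrolment figures are given as minimums, and the 40% is stated for RIFT-HPV 1 only. Part of that 40%, such as unconfirmed HPV results, may not carry over to women already counted as anal-positive. One favourable combination reaches the target: if all 30 RIFT-HPV 2 women enter by the anal route and the 39 are net of loss, 30 x 0.6 + 10.92 = 28.9. If the 39 are enrolments, the same case gives (30 + 10.92) x 0.6 = 24.6.

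Two further inferences have no support. Section 9.2.2 does not say which HPV types its rates cover, so they cannot be called any-type rates. Nor does the protocol show that multiple anogenital disease was once the entry criterion.

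What stands is that section 9.2.2 treats baseline positives as evaluable completers and gives no reason why anal pairs would escape the losses and exclusions written elsewhere in the protocol.

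**Conclusion.** The point holds as a defect in how the 28 is built. The arithmetic 18 + 10 reproduces, but it leaves no reserve for loss, so the stated 80% power for a 35% reduction is not supported.

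The size is conditional. With the 40% loss applied to all anal pairs, power is below 80% under both calibrations. With RIFT-HPV 1 taken as net of loss, it falls short under calibration A and is about 80% under B. These figures rest on carrying the 40% over to anal samples and on SDs back-solved from the protocol's own sample sizes.

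Two smaller points need no power assumption: the RIFT-HPV 1 anal rate must be reconciled between sections 4.2.1 and 9.2.2, and 28 appears in section 4.2.1 as a cohort size when it is the pooled anal target.

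**What to change.** Recalculate section 9.2.2 from:

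- the current RIFT-HPV 2 entry routes, with the expected number of women by each;
- one RIFT-HPV 1 anal rate, stated identically in sections 4.2.1 and 9.2.2;
- the HPV16/18 DNA and virion requirement of section 9.1.1.1.2;
- a stated loss for anal pairs, 40% unless another figure is justified, making clear whether the 39 is before or after loss.

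Report the resulting evaluable number with its assumed SD, power and detectable reduction. At the end of section 4.2.1, change 28 to 30 enrolled and describe 28 as the anal target pooled over both cohorts.

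The cost is revised text and probably a less favourable stated power. No added enrolment is required.
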